### Long-term follow-up at 5 years

However, it is recognised that the detection of many subtle deficits, particularly in the fields of behaviour, attention and cognition, may be unreliable at the age of two years. These deficits have major implications for educational achievement and social functioning. We therefore hope to be able to perform a detailed, standardised clinical examination and assessment of neurological, developmental, cognitive and behavioural function at the age of five years. Families will be informed during recruitment of our intention to follow up their children again.

### Sample Size

Sample size estimates have been made based on what are considered to be potentially clinically important differences in the cognitive scores from the Bayley-III at two years corrected age.

Table 1 gives a range of total sample sizes based on variations in the mean and standard deviation of these scores.

**Table 1 T1:** Sample size estimates

Assumed mean scores of the two arms	Assumed SD of Bayley-III cognitive scores	Total sample size required for 90% power	Number needed to be recruited assuming 80% survival to 2 years
85 & 95	15	94	118

85 & 95	10	42	53

90 & 95	10	168	210

The first of these options (requiring the recruitment of 118 infants) offers a realistic recruitment target whilst also giving 90% power to detect a significant difference between the two arms (at a two-tailed 5% level of significance). The choice of 85 and 95 as the two Bayley scores on which to derive the trial size is based on: a) what might be considered a clinically significant difference and b) existing knowledge of ECMO survivors [2,9].

### Feasibility

We estimate that it should be feasible to recruit this number of infants in 30 months as:

• all 4 UK ECMO centres have agreed to join the study.

• It is estimated that 70 suitable neonates will be referred to these centres per year (67% recruitment to the study is therefore required).

### Statistical Analysis

Demographic factors and clinical characteristics will be summarised with counts (percentages) for categorical variables, mean (standard deviation [SD]) for normally distributed continuous variables, or median (interquartile [IQR] or entire range) for other continuous variables.

Comparative statistical analysis will entail calculating the mean difference plus 95% confidence interval [CI] for the primary outcome (likewise for other normally distributed continuous outcomes), the median difference (plus 95% CI) for skewed continuous variables and the risk ratio (plus 95% CI) for secondary outcomes which are categorical.

For the primary analysis, patients will be analysed in the groups to which they are assigned, comparing the outcome of all babies allocated to "ECMO with cooling" with all those allocated to "ECMO" alone, regardless of deviation from the protocol or treatment received. For the primary outcome (the cognitive score from the Bayley-III at age 2 years), the analysis will compare the mean scores for each group of surviving babies. The rationale for this choice of primary analysis is to give a fair representation of the average ability of assessable children, accepting the limitation that excluding deaths might impose. There is potential for bias, but only in the presence of high and/or differential mortality between the groups. An adjusted analysis will be performed for the primary outcome to investigate the impact of stratification/known prognostic factors.

The primary analysis is therefore of survivors. Sensitivity analyses will be used to assess the robustness of the results and the impact of missing data. Missing primary outcomes data for surviving children arise due to (i) logistical reasons, (ii) parental wishes, (iii) children being untestable for behavioural reasons or (iv) children being too severely disabled to be assessed using the Bayley-III scales. Strategies employed will include:

1. imputing arbitrary scores

2. imputing scores using single imputation by using repeated random sampling from a distribution (mean = 100 SD = 15) to create a sample of scores per missing value e.g. 5, depending on the individual circumstances and impute the appropriate summary statistic i.e. the median.

For any children that we cannot see:

• but where we have some indication from parental questionnaire of no neurodevelopmental problems, we will sample randomly from those scores of children who score above -2 SDs of the mean

• but where we have no information regarding the child or there is an indication of a neurodevelopmental problem, then we would sample randomly from the entire range of scores within our study population

For any children we do see:

• but for whom we are unable to obtain a cognitive score on the Bayley-III because of behavioural difficulties, but who are motorically competent, we will sample from between 2 and 3 SDs below the mean

• but are too severely disabled to test, we will sample from between 3 and 4 SDs below the mean

NB. imputing missing values using multiple imputation techniques based on values of the population distribution (taking into account the child's most important characteristics) would be preferable, but the sample size in this study is too small.

A further sensitivity analysis will use rank based statistical methods; typically more conservative, but valid given that we are at the extremes of the distribution.

The consistency of the effect of cooling on the group of babies recruited to the trial will be explored to see whether cooling is of particular help, or not, to specific subgroups of infants, using the statistical test of interaction. Therefore pre-specified subgroup analyses include: (i) whether the ECMO is veno-arterial or veno-venous; (ii) whether the child's oxygenation index at the time of recruitment is <60 or ≥ 60; (iii) initial aEEG pattern shown on the cerebral function monitor, and (iv) primary diagnostic group. Subgroup analysis will be performed on the following outcomes (a) the primary outcome, (b) vision, (c) hearing and (d) neurological status. The subgroup analyses will be interpreted as exploratory.

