### Randomisation

All infants recruited to the study will be cared for in one of the four UK ECMO centres. Infants who require ECMO will be transferred to these centres from across the country. Babies who are thought to be eligible will be assessed by the treating clinician who will confirm eligibility, ensure that consent has been obtained and then randomise the patient using the web based system, provided by the National Perinatal Epidemiology Unit (NPEU). As soon as parental consent has been obtained, the recruiting ECMO specialist, or delegate, will log on to the web site and obtain the treatment allocation, which will be either to "ECMO" or "ECMO with cooling". Minimisation will be used to ensure balance between the groups with respect to the most important factors likely to affect later outcome, one of which is the method of cannulation (either veno-venous or veno-arterial).

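### Allocation is minimised on prognostic factors, but the primary comparison appears to be the unadjusted mean difference, so its confidence interval is somewhat too wide

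*Protocol article*

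**What the plan says.** The Randomisation section of the protocol article states: "Minimisation will be used to ensure balance between the groups with respect to the most important factors likely to affect later outcome". It names one such factor, the cannulation method (veno-venous or veno-arterial).

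The Statistical Analysis section sets the primary effect measure as a mean difference with a 95% confidence interval. For the Bayley-III cognitive score, "the analysis will compare the mean scores for each group of surviving babies". No covariate is mentioned there. The same paragraph then adds: "An adjusted analysis will be performed for the primary outcome to investigate the impact of stratification/known prognostic factors".

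The article does not use the word unadjusted. But an adjusted analysis announced separately, with the aim of seeing what the factors do to the result, implies that the primary one is unadjusted. The Sample Size section fits this reading. It works from means of 85 and 95 and a total SD of 15, with no reduction for covariates.

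**The concern.** When allocation is forced to balance a factor that predicts the outcome, that factor contributes little to the chance difference between the arms. The two-sample standard error still counts the factor's contribution as noise. The reported interval is then wider than the real uncertainty, and the test rejects a true null hypothesis less often than 5%.

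The trial takes on the work of minimisation and then leaves the resulting gain in precision out of its primary analysis. Precision is hard to buy otherwise. The Feasibility section needs 67% of suitable referrals to reach 118 infants in 30 months, and only about 94 survivors are expected to be analysed.

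The analysed children are also not the whole randomised set, because of deaths and unscored survivors. Adjustment corrects any imbalance in the measured factors among those who remain; a raw difference does not.

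**Working it through.** **Inputs from the Sample Size section.** Difference 10 points (85 against 95), SD 15, significance "at a two-tailed 5% level of significance", power 90%, 80% survival, 94 analysed and 118 recruited. **Assumptions.** Allocation 1:1, so 47 per arm analysed. R², the share of score variance explained by the minimisation factors, is not given, so a range is shown.

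**1. The plan's own figure.** Per arm, n = 2 × (1.96 + 1.282)² × 15² / 10² = 47.3, or 94.6 in total. The stated 94 agrees apart from rounding (rounding up gives 48 per arm, 96). Recruitment is 94 / 0.80 = 117.5, so 118. With 47 per arm, power is 0.898 by the normal approximation and 0.892 by the noncentral t. This reproduces the plan, on the total SD.

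**2. Nominal standard error of the unadjusted difference.** 15 × √(2/47) = 3.094. The half-width of the interval is 1.96 × 3.094 = 6.06 points.

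**3. Effect of balanced factors.** The true standard error is 3.094 × k, with k = √(1 − R²).

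- Excess width of the unadjusted interval: 1/k − 1.
- Actual type I error of the unadjusted test under exact balance: 2 × [1 − Φ(1.96/k)].
- Power of the unadjusted test under exact balance: Φ[(10/3.094 − 1.986)/k], where 1.986 is the t critical value on 92 df.
- Power of the adjusted test: noncentral t with noncentrality 10/(3.094 × k) on 89 df, assuming three binary factors.

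| Assumed R² | k | Adjusted half-width | Unadjusted interval too wide by | Type I error, exact balance | Power at 10 points, unadjusted | Power at 10 points, adjusted |
|---|---|---|---|---|---|---|
| 0.05 | 0.975 | 5.91 | 2.6% | 4.4% | 0.899 | 0.907 |
| 0.10 | 0.949 | 5.75 | 5.4% | 3.9% | 0.905 | 0.921 |
| 0.20 | 0.894 | 5.42 | 11.8% | 2.8% | 0.918 | 0.947 |

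At a true difference of 7 points and R² 0.20, unadjusted power is Φ[(7/3.094 − 1.986)/0.894] = Φ(0.309) = 0.62. Adjusted power is 0.71. At R² 0.02 the interval is only 1.0% too wide.

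**4. Check without exact balance.** I simulated minimisation with assignment probability 0.8 on three assumed binary factors. There were 118 infants, each surviving with probability 0.80 regardless of arm, and 20,000 runs per setting.

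| Assumed R² | Type I error, unadjusted / adjusted | Mean half-width, unadjusted / adjusted | Power at 10 points, unadjusted / adjusted |
|---|---|---|---|
| 0.10 | 4.1% / 5.0% | 6.14 / 5.85 | 0.902 / 0.919 |
| 0.20 | 3.5% / 5.0% | 6.13 / 5.51 | 0.909 / 0.945 |

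Shorter simulations of the same kind gave unadjusted type I errors of 4.2% to 4.4% at R² 0.10 and 3.3% to 3.6% at R² 0.20. With 2,500 runs the Monte Carlo standard error is √(0.04 × 0.96 / 2500) = 0.4 points, so these agree.

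**The case against.** An adjusted analysis of the primary outcome is already planned, so the better estimate will be produced in any case. What is at issue is which of two planned analyses carries the conclusion. The article is a condensed account and never says unadjusted. The covariates and model form may be settled in an analysis plan that is not shown. All of this stands, and it makes the point small. It does not remove it, because the article itself says which comparison is primary and which is additional.

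Four stronger readings are tempting, and the documents do not support them.

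- *The trial is underpowered.* The sample size uses the total SD of 15, so an unadjusted comparison matches its own calculation and keeps about 90% power. Power is lost only relative to the adjusted analysis.
- *Adjustment lifts power from 0.892 to 0.921 or 0.947.* The 0.892 belongs to a test without forced balance. Under balance the unadjusted test gains too, to about 0.90 to 0.92, so the gain at 10 points is about 2 to 3 percentage points at R² 0.10 to 0.20.
- *Type I error is really 3.9% or 2.8%.* Those values need exact balance among the children analysed. Imperfect minimisation and deaths loosen it, and the error moves back towards 5%. The more balance is lost, the nearer the unadjusted standard error is to being right.
- *The factors are known to be strong.* The article calls them the most important, names one and gives no strength for a two-year cognitive score in survivors. R² could be close to zero.

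**Conclusion.** The point holds as a matter of efficiency; it does not threaten validity. On the natural reading, the primary interval ignores balance that the design creates, so it is somewhat too wide and its test conservative. False positives are not inflated and the stated power is not missed.

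The size rests on an assumed R². The interval is about 3%, 5% and 12% too wide at R² 0.05, 0.10 and 0.20. Allowing for imperfect minimisation and 20% deaths, type I error is about 4.1% to 4.4% at R² 0.10 and 3.3% to 3.6% at R² 0.20. The power gain from adjustment is 1 to 3 percentage points at the design difference and about 9 points at a 7-point difference with R² 0.20. If the factors hardly predict the score, the gain is negligible.

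**What to change.** In the Statistical Analysis section, define the primary estimate as the treatment coefficient, with its 95% confidence interval, from a linear model of the Bayley-III cognitive score. The model should contain arm and the minimisation factors as entered at randomisation, including cannulation method. Report the unadjusted mean difference as supportive. Any further prognostic factors can stay in the additional adjusted analysis already planned.

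Fixing this order in advance also avoids a dispute if the two intervals fall on opposite sides of zero.

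The cost is wording and a few degrees of freedom. With three binary factors, for example, the residual degrees of freedom go from 92 to 89 and the critical value from 1.986 to 1.987. No new data are needed, because the factors are already recorded at randomisation, and the sample size need not change.

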### Ethics Approval

Ethics approval was granted by the Trent Research Ethics Committee of the UK National Research Ethics Service (reference: 05/MRE04/22).

### Organisation

#### Project management group

A core team of individuals will liaise regularly regarding the general progress and management of the study. This will normally occur by teleconference every 6 weeks. Trial Steering Committee meetings will occur annually. A central co-ordinating centre based at the National Perinatal Epidemiology Unit will be responsible for organising these meetings as well as:

• General oversight and compliance with procedures;

• Data management;

• Data analysis;

• Servicing the Data Monitoring Committee;

• Organising follow up appointments and maintaining contacts with families via newsletters and birthday cards.

#### Data Monitoring Committee

This will be independent of the study organisers and will meet annually. During the period of recruitment to the study, interim analyses will be supplied, in strict confidence, to the DMC, together with any other analyses the DMC may request. The data will be supplied to the Chair of the DMC as frequently as she requests. Meetings of the committee will be arranged periodically, as considered appropriate by the Chair. In the light of interim data, and other evidence from relevant studies (including updated overviews of the relevant randomised controlled trials), the DMC will inform the Steering Committee, if in their view i) there is proof beyond reasonable doubt that the data indicate that any part of the protocol under investigation is either clearly indicated or contra-indicated, either for all infants or for a particular subgroup of trial participants or ii) it is evident that no clear outcome will be obtained.

Appropriate criteria for proof beyond reasonable doubt cannot be specified precisely. A difference of at least 3 standard errors in the interim analysis of a major endpoint may be needed to justify halting, or modifying, such a study prematurely. If this criterion were to be adopted, it would have the practical advantage that the exact number of interim analyses would be of little importance. One interim analysis is planned for each year of recruitment, as well as one analysis six months after recruitment has stopped. These analyses will concentrate on outcomes at hospital discharge, as many of these babies will not have had their two-year assessments performed at the time of the interim analyses. Unless modification or cessation of the protocol is recommended by the DMC, the Trial Steering Committee, collaborators and administrative staff (except those who supply the confidential information) will remain ignorant of the results of the interim analysis. Collaborators and all others associated with the study may write through the NEST Co-ordinating Centre to the DMC to draw attention to any concern they may have about the possibility of harm arising from the treatment under study, or about any other matters that may be relevant.

The membership is:

[name] (Chair), [name] Evaluation, LSHTM, London

[name], Director of PIC, Royal Brompton Hospital, London

[name], Consultant Paediatrician, Royal Maternity Hospital, Belfast

[name], Consultant Paediatrician, Liverpool Women's Hospital.

#### Assessment of Safety

Safety monitoring has been delegated by the Sponsor (University Hospitals of Leicester NHS Trust, of Leicester) to the National Perinatal Epidemiology Unit (NPEU) at the University of Oxford.

Safety will be assessed continuously during each baby's stay in the ECMO unit. Any adverse events which require expedited reporting will follow the system outlined below.

Other outcomes, which may also be considered safety outcomes, such as early neonatal morbidity, but which are anticipated outcomes for this group of babies, will be captured on study specific data collection forms.

#### Expected Adverse Drug Reactions

No adverse drug reactions will occur as the study intervention is not a drug.

#### Expected Serious Adverse Events (SAEs)

The following are serious adverse events that could be reasonably expected for this group of babies during the course of the study:

• Death

• Major ECMO circuit complications such as oxygenation failure of line rupture

• Major cerebral haemorrhages after trial entry

• Major haemorrhage requiring transfusion

For the purposes of this study these SAEs require immediate reporting.

#### Serious Adverse Reactions (SARs)

Although the study intervention is not a drug, the only theoretically possible recognised adverse reactions/events associated with this treatment are:

• Deranged clotting arising during cooling period

• Evidence of impaired immunity arising during cooling period

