#### Feasibility studies for hypothermia in infants having ECMO

Although there is some information about the physiological impact of mild hypothermia [33°C or above) data applicable to the newborn are very limited. More information is available in relation to moderate hypothermia in adults but this is only helpful in identifying those bodily functions that might be impaired by a period of mild hypothermia [28-30]. No systematic studies have previously been performed to assess the therapeutic affect of mild hypothermia on patients on ECMO. Therefore in preparatory work (funded by The British Heart Foundation) we have investigated the feasibility and safety of using mild hypothermia in neonates receiving ECMO. The study population of this investigation compromised the following infants (note the next reduction in temperature or increase in duration of hypothermia only occurred after the successful completion of the previous stage):(Neonatal patients were defined as infants of less than 28 days of age).

5 neonates maintained at 37°C throughout their ECMO course (controls);

5 neonates maintained at 36°C for the first 12 hours of their ECMO course;

5 neonates maintained at 35°C for the first 12 hours of their ECMO course;

5 neonates maintained at 34°C for the first 12 hours of their ECMO course.

5 neonates maintained at 37°C throughout their ECMO course (controls);

5 neonates maintained at 36°C for the first 24 hours of their ECMO course;

5 neonates maintained at 35°C for the first 24 hours of their ECMO course;

5 neonates maintained at 34°C for the first 24 hours of their ECMO course.

5 neonates maintained at 34°C for the first 48 hours of their ECMO course.

The decision to use ECMO was based on standard criteria and was made on clinical grounds alone (an oxygenation index of 40 or more, or a PaCO_2_of 13 kPa or more despite maximal non-ECMO support and with no contra-indication to ECMO).

The clinical course of each infant was closely scrutinised but in addition a number of specific investigations and observations were performed in relation to: blood clotting, immune function, EEG, cardiac conduction, oxygenator function and circuit performance.

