A paper describing the first 20 patients [31] and a second paper focusing on the next 25 patients have been published [3]. In summary, there was no evidence that hypothermia had an adverse impact on the acute clinical condition of the baby. There did appear to be an effect on cardiac conduction as measured by ECG, but this was not clinically apparent during the baby's ECMO course. There was no suggestion of an excess of haemorrhagic complications. Similarly there was no adverse effect noted in relation to the ECMO circuit or its management. Of particular relevance to long term outcome, temperature change had no effect on the aEEG.

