#### Expedited/immediate reporting of safety events

All expected SAEs or SARs described above must be reported to the Trial Co-ordinating Centre within 10 days of discovery or notification of the event, this will be immediately referred to the Chief Investigator or his delegated deputy. If urgent safety measures will be required as a result of an SAE or SAR then the event or reaction must be reported within one working day of discovery or notification of the event to the Trial Co-ordinating Centre. A Standard Operating Procedure (SOP) outlining the reporting procedure for clinicians will be provided on the reverse of the SAE form. An SOP will also be available as part of the Trial Specific SOPs which will outline the reporting procedure for the Trial Co-ordinating Centre. All SAE and SAR information must be recorded on an SAE form and faxed to the Chief Investigator or their delegated Deputy. Additional information received for a case (follow-up or corrections to the original case) needs to be detailed on a new SAE and SAR form and faxed to the Chief Investigator or their delegated deputy.

The severity of events will be assessed on the following scale: 1 = mild, 2 = moderate, 3 = severe. The relationship of SAEs or SARs to the study intervention will be assessed according to the definition provided above.

The Trial Co-ordinating Centre will report all SAEs and SARs to the Ethics Committee concerned using the SAE report form for non-CTIMPs, available from the NRES website. In addition a copy of the SAE or SAR will be forwarded to the Chair of the Data Monitoring Committee. The Chair will also be provided with a document detailing all previous SAEs and SARs. The Chief Investigator will also inform all investigators concerned of relevant information about SAEs and SARs that could adversely affect the safety of participants.

In addition to the expedited reporting above, the Chief Investigator shall submit, once a year throughout the clinical trial, or on request, a safety report to the Ethics Committee.

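### The list of reactions to cooling is worded as exhaustive but omits cardiac conduction, where the trial's own pilot saw an apparent ECG effect, so a serious conduction event is not a listed trigger for the 10-day report

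*Protocol article*

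**What the plan says.** All references are to the protocol article.

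- **Serious Adverse Reactions (SARs).** The section says "the only theoretically possible recognised adverse reactions/events associated with this treatment are" two: deranged clotting and impaired immunity, each arising during the cooling period.
- **Feasibility studies for hypothermia in infants having ECMO.** The pilot made specific observations of "blood clotting, immune function, EEG, cardiac conduction, oxygenator function and circuit performance". The summary of results then says "There did appear to be an effect on cardiac conduction as measured by ECG", and continues "but this was not clinically apparent during" the ECMO course. It reports no suggestion of excess haemorrhage, no adverse effect on the circuit and no effect on the aEEG.
- **Expected Serious Adverse Events (SAEs).** Four items are listed: death, major circuit complications, major cerebral haemorrhage after trial entry, and major haemorrhage needing transfusion. The section adds "For the purposes of this study these SAEs require immediate reporting".
- **Expedited/immediate reporting of safety events.** The main duty on sites reads "All expected SAEs or SARs described above must be reported to the Trial Co-ordinating Centre within 10 days", counted from when the event is discovered or notified. A one-working-day rule follows: "If urgent safety measures will be required as a result of an SAE or SAR", the event goes to the Co-ordinating Centre within that time. The Centre passes SAEs and SARs to the Ethics Committee and copies them to the DMC Chair, with a document of all previous ones.
- **Reporting procedures for all adverse events.** Every adverse event goes on the data collection form, with no time limit stated.

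**The concern.** The article states a closed list that its own pilot result does not fit. Of the three bodily functions at issue (clotting, immunity, conduction), the pilot set out to measure all three. Conduction is the only one for which the article reports an apparent effect, and it is the one left off the list.

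This matters because the list also defines a reporting trigger. If sites read the 10-day duty as limited to the named events, a serious rhythm or conduction event during cooling may reach the Co-ordinating Centre only through routine data collection. The cumulative SAE and SAR document held by the DMC Chair could then show few or no cardiac events because of how the list is drawn. The trial also allows cooling for longer than any pilot stage at 34°C, so an effect seen only on ECG in the pilot is one the DMC would want to follow.

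**Working it through.** This is mainly a comparison of text. The article gives no figure to reproduce.

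**1. Is the exclusivity claim consistent with the pilot?** No. The SAR section speaks of what is theoretically possible and recognised. The feasibility section itself recognises an apparent effect of hypothermia on conduction. That the effect was subclinical bears on how often it might become serious, not on whether it is possible.

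**2. Is a conduction event on either list?** No. The SAR list has two items and the expected SAE list has four. None is cardiac, except that a fatal event would be reported as a death.

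**3. Which duties depend on the lists?**

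| Clause | Limited to listed events? |
|---|---|
| 10-day report from the site to the Co-ordinating Centre | Yes, by its reference to events described above |
| One-working-day report | No, but only if urgent safety measures are needed |
| Onward report to the Ethics Committee, and copy to the DMC Chair | Not worded as limited |
| Data collection form | No, but no time limit |

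The onward duties are worded broadly, but the Centre can forward only what sites send. Sites have an explicit timed duty for listed events and for events that need urgent safety measures. A serious, non-fatal conduction event needing no such measure falls between the two. The Causality Assessment section does not close the gap, because it says only that a case judged causally related qualifies as an Adverse Event.

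**4. How much reassurance does the pilot give?** Inputs are the pilot group sizes in the feasibility section, and the assumption that *not clinically apparent* means zero clinical events. The one-sided 95% upper limit for 0 events in n infants is 1 − 0.05^(1/n).

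| Pilot infants | n | Upper limit |
|---|---|---|
| Held at 34°C for 48 hours | 5 | 1 − 0.05^(1/5) = 45% |
| Held at 34°C for 12, 24 or 48 hours | 5 + 5 + 5 = 15 | 1 − 0.05^(1/15) = 18% |
| Cooled to any temperature (34, 35 or 36°C) | 7 × 5 = 35 | 1 − 0.05^(1/35) = 8% |

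The second row matches the trial's target temperature. No pilot infant was cooled for longer than 48 hours, while the trial allows 72.

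**5. Scale in the trial.** With 118 infants in two arms, about 118/2 = 59 are cooled. The documents give no rate of clinically important rhythm or conduction events. If it were 5% to 10% (an assumption), 0.05 × 59 ≈ 3 to 0.10 × 59 ≈ 6 such events would occur in the cooled arm. Some would be reported anyway because they were fatal or needed urgent measures, so 3 to 6 overstates the number left without a listed trigger.

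**The case against.** The strongest reply has four parts.

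**The pilot effect was subclinical.** The SAR section concerns serious, recognised reactions, and an ECG change that was not clinically apparent need not be one. The article also reports no evidence of harm to the infants' acute condition. This stands as a limit on how alarming the signal is. It does not rescue a statement that nothing else is theoretically possible.

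**Other routes exist.** A reader might infer that a conduction signal has no expedited route to the DMC Chair, or that it could only ever be recorded as a general adverse event. The article does not support that. The one-working-day clause, the duty to report all SAEs and SARs onward and the copy to the Chair are not tied to the lists. A death is reportable. The Data Monitoring Committee section lets the Chair receive data as often as requested, plans yearly interim analyses during recruitment, and lets anyone associated with the study raise concerns about harm. This stands in full: the route is ambiguous, not absent. A request does, however, depend on the Chair knowing to ask.

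**The gap is general.** The reporting section does not say whether any unlisted serious event falls under the 10-day rule, so a single cardiac line would not cure it. This also stands, and the fix addresses it.

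**An article condenses, and the reporting SOPs are not shown.** That would answer a complaint about missing detail. Here the article makes a positive statement that its own pilot summary does not fit.

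**Conclusion.** The point holds in this form: the SAR section claims an exhaustive list that omits the conduction effect reported from the trial's own pilot, and the 10-day duty is tied to the listed events. A serious conduction event during cooling that needs no urgent safety measure is therefore not a listed trigger, and whether it reaches the DMC Chair promptly is unclear from the text.

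The text comparison rests on no numerical assumption. The 18% limit assumes zero clinical events among the 15 infants at 34°C. It measures how little the pilot can exclude and does not estimate the true rate. The figure of 3 to 6 events is illustrative, and the conclusion does not depend on it. The issue concerns safety oversight and is worth correcting. It does not touch the sample size, the type I error rate or the primary analysis.

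**What to change.** Reconcile the feasibility, SAR and expedited-reporting sections:

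1. In the SAR section, remove the claim that the listed reactions are the only theoretically possible ones.
2. Add clinically important arrhythmia or conduction disturbance to the reportable events. Collect it identically in both arms and tabulate it by arm for the DMC.
3. In the expedited-reporting section, state that serious events not on the lists are reported on the same timeline as those that are.

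The cost is a line on the SAE form, a row in the DMC tables and a few more SAE reports. Adverse events are already recorded on the data collection form, so no new collection procedure is needed. Clinical management does not change.
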